## Background

Falls constitute one of the most common and serious public health problems in older populations. Fall incidents are associated with considerable morbidity and mortality [1-3]. Even a low energetic trauma, such as an unintended fall, can lead to major injuries in older adults with long-term consequences [4,5]. The incidence of falls and the severity of fall-related complications rises steeply beyond the age of 65 years [1,2,4-6]. Approximately 72,000 older adults visit an Emergency Department in the Netherlands each year due to a fall. Over 30,000 are hospitalized, and nearly 1,600 elderly die due to a fall per year [7,8]. The large burden of fall-related healthcare consumption is leading to high healthcare costs in western societies [5,9,10]. Over the past decades several risk factors for falls have been identified. Major risk factors include one or more previous falls, mobility impairments, high age, and the use of fall-risk increasing drugs [11,12]. The majority (73%) of older persons use one or more drugs [13]. In 2008, nearly half of all drug prescriptions in the Netherlands were delivered to persons aged 65 years and older who constituted only 15% of the Dutch population in that year [14]. Adverse Drug Reactions are frequently seen in older adults [15]. A meta-analysis of observational studies showed an increased fall risk with certain drug groups, i.e., psychotropic [16] and cardiovascular drugs [17]. Approximately three-quarters of the community dwelling elderly used at least one prescribed drug, and about a third used at least one fall-risk increasing drug [13].

There is evidence that withdrawal, reduction, or substitution of fall-risk increasing drugs can reduce fall risk in older adults. Only one small, randomized controlled trial on drug withdrawal has been performed [18]. Campbell *et al. *found that withdrawal of psychotropic medication significantly reduced the risk of falling, but permanent withdrawal proved very difficult to achieve. Therefore the authors made recommendations for a larger randomized controlled trial (RCT) to study the single effect of drugs assessment and drugs modification on fall risk. A recent prospective cohort study with a two-month follow-up period showed that the withdrawal of fall-risk increasing drugs was associated with a reduction in falls [19].

Furthermore, an increased susceptibility to certain adverse drug reactions may partly be due to genetic polymorphisms that alter responses of individual persons to various drugs [13]. A possible cause might be the pathway of hepatic drug metabolization by the cytochrome P-450 family of biotransformation enzymes [20]. Consequently, poor, extensive and ultra-rapid metabolizers for certain cytochrome pathways and membrane bound transporters can be distinguished [21], which influence the pharmacodynamics and pharmacokinetics. The majority of fall-risk increasing drugs are metabolized by a small number of enzymes, the major ones being CYP450 2D6, 2C9, 2C19 and 3A4/5 [22]. Due to polypharmacy among older adults, the risk of a CYP 450 interaction increases.

A systematic fall-related drugs assessment combined with medication changes and a one-year follow-up assessment among older fallers may contribute to a reduction in the incidence of new falls and related consequences [19]. At this moment a structured medication assessments are not part of standard care of older fallers presenting at the Emergency Department. In the Netherlands, the current care of fall-related injuries consists of treatment of the injuries of the fall. However, before a systemic fall-related medication assessment can be incorporated in the routine work-up of older persons presenting with a fall, further evidence is required. The aim of this randomized controlled trial is to compare the effect of withdrawal of fall-risk increasing drugs versus 'care as usual' on future falls. The primary outcome of this study is be the number of new falls and fallers. Secondary outcome measurements are possible health effects of medication withdrawal, health-related quality of life, costs, and cost-effectiveness of the intervention.

## Methods/Design

The study is designed as a multicenter RCT with a one-year follow-up period in the Netherlands. The Medical Ethics review board of the Erasmus MC, University Medical Center, approved the study protocol. The study started in October 2008. The flow chart is shown in Figure 1.

**Figure 1 F1:**
[figure not shown]
**Flow chart**.

### Study population

Patients aged 65 years and over, who visit the Emergency Department of a participating hospital due to a fall, are eligible for inclusion. A fall is defined as coming to rest unintentionally on the ground or a lower level with or without losing consciousness, but not induced by acute medical conditions, *e.g*., stroke, or exogenous factors such as a traffic accident [23].

Patients meeting the following inclusion criteria are eligible for enrollment:

1. Aged 65 years or older (no upper age limit)

2. Attended the Emergency Department due to a fall incident

3. Taking one or more fall-risk increasing drugs for at least two weeks prior to the fall

4. Mini-Mental State Examination score of 21/30 points or over

5. Able to walk independently

6. Community dwelling

7. Provision of informed consent by patient

If any of the following criteria applies, patients will be excluded:

1. Patient participation in another trial

2. Fall not meeting criteria of specified definition

3. Likely problems, in the judgment of the investigators, with maintaining follow-up (e.g., patients with no fixed address)

4. Not willing to complete the research protocol (such as attending at a follow-up visit)

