### Procedure

All persons visiting the Emergency Department due to a fall receive care as usual for their injuries. Within two weeks following the Emergency Department attendance, patients are contacted by telephone with information about the study. All eligible study participants will receive written information about the study and all interested patients will receive an appointment for the research outpatient clinic. The visits to the outpatient clinic take place within two months after Emergency Department attendance. If the patient meets all eligibility criteria and no exclusion criteria are present at the research outpatient clinic, the patient will be asked to sign the Informed Consent Form before the study procedures take place. Patients who do not meet the inclusion criteria will be excluded. During the outpatient clinic visit a record is made of the falls risk profile (FRP), falls history, health-related quality of life (HRQoL) and physical performance are measured of all study participants. Furthermore, a geriatric assessment and a standardized medication assessment will take place. Eligible patients will be randomized to one of the treatment arms, the intervention group versus 'care as usual'. The aim in the intervention group will be to reduce fall-risk increasing drugs, and in the 'care as usual' group no (medication) change will be made. All included participants receive a Falls Calendar for reporting falls during a one-year follow-up period as well as a cost-evaluation form at three, six, nine and twelve months after the first research outpatient clinic visit. One year after the first visit, the study participants are invited for a final visit to the research outpatient clinic in order to reassess the FRP, falls history, HRQoL, and physical performance. Adherence to their medication is also evaluated. After the final visit to the outpatient clinic a brief letter concerning the study start and completion will be sent to the patient's General Practitioner. Table 1 shows the schedule of events of this study.

**Table 1 T1:** Schedule of events

	Screening	1^st ^visit	3 months	6 months	9 months	12 months
Telephone call	X					
Information package	X					
Informed Consent		X				
Randomization		X				
Baseline data		X				
EQ-5D		X				X
SF-12		X				X
FRP		X				X
Orthostatic hypotension test		X				X
Complications			X	X	X	X
Falls calendar			X	X	X	X
Healthcare consumption			X	X	X	X
ADL		X				X
Physical functioning (VAS)		X				X

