### Intervention

The single intervention will consist of a systematic fall-related medication assessment combined with drug withdrawal or modification, if safely possible. Fall-risk increasing drugs, as defined in the literature [16,17,19,24], will be stopped, reduced or substituted with potentially safer drugs in the intervention group. A complete list of fall-risk increasing drugs, based on current literature, is shown in Table 2.

**Table 2 T2:** Drugs classified as fall-risk increasing drugs in the IMPROveFALL study

Category	Drug type
Central nervous system	**anxiolytics/hypnotics **(benzodiazepines and others); **antidepressants (**tricyclic antidepressants, selective serotonin reuptake inhibitors, serotonin-norepinephrine reuptake inhibitors and monoamine oxidase inhibitors), **neuroleptics **(dopamine D2-receptor agonists and serotonin dopamine receptor antagonists)

Cardiovascular	**Antihypertensives **(diuretics, beta-adrenoceptor blockers, alpha-adrenoceptor blockers, centrally acting antihypertensives, calcium channel blockers, angiotensin converting enzyme inhibitors and angiotensin receptor blockers); **Anti-arrhythmic drugs **(Antiarrhythmics, nitrates, digoxin, vasodilators)

Anti-inflammation	NSAIDs

Gastro-Intestinal	Antacids (H-2 receptor antagonists)

Analgesics	Opioids

Pulmonary	Sympathomimetics, anti-histaminics

Diuretics	Thiazide diuretics, loop diuretics

For each drug, the clinical investigator will assess whether the initial indication still exists. Proposed changes in medication will be discussed with a senior geriatrician and the participant's General Practitioner and with the prescribing doctor if other than the General Practitioner. If consensus is obtained, fall-risk increasing drugs will be discontinued when considered redundant, reduced in dose over a one-month period, if safely possible, or substituted for potentially safer drugs if necessarily and available. For each drug modification, the clinical investigator will follow the standardized instructions of the Dutch National Formulary [25], and a clinical pharmacologist will be available for advice when needed. A research nurse will offer counseling and evaluate possible negative effects by weekly telephone calls over a period of 1 month, and discuss any problems with the clinical investigator and the geriatrician (project leader).

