### Measurements

### Medication use

Medication use will be assessed by registering the drug names directly from the medication packaging. For each drug, both prescription and over-the-counter (OTC), the name, intake frequency, dosage, start and stop dates, and whether the drug was prescribed before or after the fall will be registered. The information will be verified and compared with data retrieved from the patients' General Practitioner and local pharmacist.

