### Sample size calculation

A total number of 620 patients will be included in the study, 310 in the control group and 310 in the intervention group. Calculation of the required sample size is based on the assumption that the annual cumulative incidence of further falling is 50% without intervention [40], a 15% drop-out (including death) [11], drug withdrawal being possible in 50% of the participants in the intervention group and a 50% decrease of further falls among participants with successful withdrawal [18]. A single-sided test with an alpha level of 0.05 and a beta of 0.2 indicates that 310 patients in both groups is sufficient in order to detect a 25% decrease of respondents reporting further falls in the intervention group.

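### Eligibility depends on drug use before the fall, not at randomization up to two months later, so a patient with no fall-risk drug left to withdraw can be randomized and can only dilute the effect

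*Protocol article*

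**What the plan says.** All references are to the protocol article.

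- **Study population**, inclusion criterion 3: "Taking one or more fall-risk increasing drugs for at least two weeks prior to the fall". None of the other six inclusion criteria or the four exclusion criteria concerns drug use.
- **Procedure**: "The visits to the outpatient clinic take place within two months after Emergency Department attendance". Table 1 places consent and randomization at this first visit. Eligibility is confirmed there: "If the patient meets all eligibility criteria and no exclusion criteria are present at the research outpatient clinic", the patient is asked to consent. A medication assessment is listed among the activities of the same visit, ahead of the sentence on randomization.
- **Intervention**: "Fall-risk increasing drugs, as defined in the literature [16,17,19,24], will be stopped, reduced or substituted with potentially safer drugs in the intervention group". In the usual-care arm no medication change is made (Procedure).
- **Medication use**: for each drug, "start and stop dates, and whether the drug was prescribed before or after the fall will be registered".
- **Sample size calculation**: "the annual cumulative incidence of further falling is 50% without intervention", and "drug withdrawal being possible in 50% of the participants in the intervention group".
- **Statistical analysis**: the primary analysis is by intention to treat.

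**The concern.** The trial asks what happens when fall-risk increasing drugs are withdrawn compared with being left in place. Criterion 3 is meant to ensure that there is something to withdraw, but it looks back from the fall, and up to two months can pass before allocation. In that time a course may end, or the patient or a doctor may stop a drug. Table 2 includes NSAIDs, opioids and hypnotics, which can be taken for limited periods.

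The check at the clinic applies the same criterion, so a patient who has since stopped every Table 2 drug still passes on its wording. For that patient the two arms receive the same drug management. Intention-to-treat analysis rightly keeps the patient in, where he or she can contribute only a null effect. What is at stake is power and the size of the estimated effect.

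**Working it through.** **Inputs** (Sample size calculation): control risk 50%; withdrawal in 50%; risk halved when withdrawal succeeds; 15% drop-out; 310 per arm; one-sided alpha 0.05; beta 0.2.

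**Planned effect.** Intervention risk = 0.50 × (1 − 0.50 × 0.50) = 0.375, a 25% relative decrease.

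**The plan's own figure.** With the pooled-variance formula for two proportions, then division by 0.85, the stated one-sided test needs 194 / 0.85 = 229 per arm, or 210 / 0.85 = 248 with continuity correction. Two-sided without correction gives 247 / 0.85 = 291. Only two-sided with correction comes to the printed 310: 262 / 0.85 = 309. That mismatch is a separate matter. Here it means that 310 leaves some reserve on the stated one-sided test.

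**Power formula.** With n evaluable per arm, d = p1 − p2 and p̄ = (p1 + p2)/2:

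power = Φ{ [d − z·√(2p̄(1 − p̄)/n)] / √[(p1(1 − p1) + p2(1 − p2))/n] }

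Here n = 310 × 0.85 = 263.5 and z = 1.645 one-sided. For 0.50 against 0.375: (0.125 − 1.645 × 0.0432) / 0.0429 = 1.26, so power is 89.6%.

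**Affected share q.** The documents give none, so q is an assumed range. The control risk is taken as 50% with or without a drug left, also an assumption.

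*Reading A: the 50% refers to those who still use a drug.* Then p2 = 0.50 × [1 − 0.25 × (1 − q)].

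| q (assumed) | p2 | Relative decrease | One-sided power | Two-sided power |
|---|---|---|---|---|
| 0% | 37.5% | 25% | 89.6% | 82.6% |
| 5% | 38.1% | 23.8% | 86.6% | 78.6% |
| 10% | 38.75% | 22.5% | 83.2% | 74.0% |
| 20% | 40.0% | 20% | 74.7% | 63.6% |

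Power falls below 80% at q of about 14% one-sided, or about 3.4% two-sided.

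*Reading B: the 50% is over all intervention participants, as printed.* These patients are then already counted. The overall risk stays 37.5%, power stays 89.6% one-sided, and the sample size is unaffected. The implied withdrawal share among current users is 0.50 / (1 − q): 52.6%, 55.6% and 62.5% at q = 5%, 10% and 20%.

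**Does leaving these patients out help, even without replacement?** At q = 10%, n = 263.5 × 0.90 = 237.15 per arm.

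- Reading A: 0.50 against 0.375 gives 86.6% one-sided, against 83.2% with them included.
- Reading B: p2 = 0.50 × (1 − 0.50 × 0.556) = 0.361, giving 92.3% one-sided, against 89.6% with them included.

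Leaving them out gives more power under both readings.

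**The case against.** The strongest objection is that the sample size already allows for failed withdrawal, and its denominator is all intervention participants. Taken literally, a patient with nothing left to withdraw is inside the half in whom withdrawal is not expected, and the dilution table under reading A counts that patient twice. This stands: a reader might infer that these patients come on top of the assumed 50% and leave the trial underpowered, but the documents do not show that. The sample size section does not say explicitly that the 50% includes them, so the point stays open rather than settled.

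Second, the share may be small. The Background says that "structured medication assessments are not part of standard care of older fallers presenting at the Emergency Department", so stopping a drug because of the fall is unlikely to be systematic. Much of Table 2 consists of drugs commonly taken long term, such as antihypertensives and antidepressants, and a patient must have stopped all of them to have nothing left. The two-week minimum also removes the shortest courses. These arguments limit the size; they do not exclude the case.

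Third, criterion 3 uses the present tense and eligibility is confirmed at the clinic, so it could be read as requiring current use with a minimum prior duration. That reading is possible but not clear, since the only time point named is the fall.

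Finally, a reader might infer bias. There is none: the status arises before allocation, so randomization balances it in expectation.

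**Conclusion.** The point holds as a weakness in the wording of eligibility. A patient with no Table 2 drug left can be randomized, and such patients dilute the effect without biasing the comparison. The size is unknown. If the 50% withdrawal share refers to current users, 10% affected costs about 6 percentage points of power on the stated one-sided test (89.6% to 83.2%), still above the planned 80%. If it covers everyone randomized to the intervention, nothing is lost against the plan, though power that an entry check would gain is forgone. Both results rest on an assumed affected share, the protocol's own effect assumptions, and the same fall risk in patients with and without a drug left. The recommendation does not depend on which reading is right; a claim of inadequate power would.

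**What to change.** Extend criterion 3 so that the patient must also be using at least one Table 2 drug at the first research clinic visit, confirmed before randomization from the medication record already taken there. State in the sample size section whether the 50% withdrawal share covers all intervention participants or only current users.

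For patients already randomized, specify a supporting analysis limited to those using a Table 2 drug at randomization, identified from the recorded start and stop dates. Because this status is fixed before allocation, the subset comparison remains randomized. Keep intention-to-treat on all randomized patients as primary.

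The cost is a slightly smaller eligible pool and a minor amendment during recruitment, which began in October 2008. Patients enrolled before and after the amendment will have entered under slightly different criteria; the supporting analysis puts both on the same footing. No new data collection is needed.

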### Procedure

All persons visiting the Emergency Department due to a fall receive care as usual for their injuries. Within two weeks following the Emergency Department attendance, patients are contacted by telephone with information about the study. All eligible study participants will receive written information about the study and all interested patients will receive an appointment for the research outpatient clinic. The visits to the outpatient clinic take place within two months after Emergency Department attendance. If the patient meets all eligibility criteria and no exclusion criteria are present at the research outpatient clinic, the patient will be asked to sign the Informed Consent Form before the study procedures take place. Patients who do not meet the inclusion criteria will be excluded. During the outpatient clinic visit a record is made of the falls risk profile (FRP), falls history, health-related quality of life (HRQoL) and physical performance are measured of all study participants. Furthermore, a geriatric assessment and a standardized medication assessment will take place. Eligible patients will be randomized to one of the treatment arms, the intervention group versus 'care as usual'. The aim in the intervention group will be to reduce fall-risk increasing drugs, and in the 'care as usual' group no (medication) change will be made. All included participants receive a Falls Calendar for reporting falls during a one-year follow-up period as well as a cost-evaluation form at three, six, nine and twelve months after the first research outpatient clinic visit. One year after the first visit, the study participants are invited for a final visit to the research outpatient clinic in order to reassess the FRP, falls history, HRQoL, and physical performance. Adherence to their medication is also evaluated. After the final visit to the outpatient clinic a brief letter concerning the study start and completion will be sent to the patient's General Practitioner. Table 1 shows the schedule of events of this study.

**Table 1 T1:** Schedule of events

	Screening	1^st ^visit	3 months	6 months	9 months	12 months
Telephone call	X					
Information package	X					
Informed Consent		X				
Randomization		X				
Baseline data		X				
EQ-5D		X				X
SF-12		X				X
FRP		X				X
Orthostatic hypotension test		X				X
Complications			X	X	X	X
Falls calendar			X	X	X	X
Healthcare consumption			X	X	X	X
ADL		X				X
Physical functioning (VAS)		X				X

EQ-5D, EuroQol 5-D questionnaire; SF-12, Short Form-12; FRP, Fall Risk Profile; ADL, Activities of Daily living; VAS, Visual Analogue Scale.

### Randomization

Participants will be allocated to one of two treatment arms using a web-based randomization program that will be available 24 hours a day. Variable block randomization will be accomplished via a trial website. Allocation will be random. It is not possible to blind the geriatrician and patients for the allocation of the study group.

### Intervention

The single intervention will consist of a systematic fall-related medication assessment combined with drug withdrawal or modification, if safely possible. Fall-risk increasing drugs, as defined in the literature [16,17,19,24], will be stopped, reduced or substituted with potentially safer drugs in the intervention group. A complete list of fall-risk increasing drugs, based on current literature, is shown in Table 2.

**Table 2 T2:** Drugs classified as fall-risk increasing drugs in the IMPROveFALL study

Category	Drug type
Central nervous system	**anxiolytics/hypnotics **(benzodiazepines and others); **antidepressants (**tricyclic antidepressants, selective serotonin reuptake inhibitors, serotonin-norepinephrine reuptake inhibitors and monoamine oxidase inhibitors), **neuroleptics **(dopamine D2-receptor agonists and serotonin dopamine receptor antagonists)

Cardiovascular	**Antihypertensives **(diuretics, beta-adrenoceptor blockers, alpha-adrenoceptor blockers, centrally acting antihypertensives, calcium channel blockers, angiotensin converting enzyme inhibitors and angiotensin receptor blockers); **Anti-arrhythmic drugs **(Antiarrhythmics, nitrates, digoxin, vasodilators)

Anti-inflammation	NSAIDs

Gastro-Intestinal	Antacids (H-2 receptor antagonists)

Analgesics	Opioids

Pulmonary	Sympathomimetics, anti-histaminics

Diuretics	Thiazide diuretics, loop diuretics

For each drug, the clinical investigator will assess whether the initial indication still exists. Proposed changes in medication will be discussed with a senior geriatrician and the participant's General Practitioner and with the prescribing doctor if other than the General Practitioner. If consensus is obtained, fall-risk increasing drugs will be discontinued when considered redundant, reduced in dose over a one-month period, if safely possible, or substituted for potentially safer drugs if necessarily and available. For each drug modification, the clinical investigator will follow the standardized instructions of the Dutch National Formulary [25], and a clinical pharmacologist will be available for advice when needed. A research nurse will offer counseling and evaluate possible negative effects by weekly telephone calls over a period of 1 month, and discuss any problems with the clinical investigator and the geriatrician (project leader).

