### Outcome measures

The primary outcome measure will be the incidence of new falls, fallers, based on the Falls Calendar. Secondary outcome measures will be fall-related injuries, generic health-related HRQoL, compliance, quality adjusted life years (QALY), genetic polymorphisms associated with increased adverse drug reactions, and positive or negative health effects, cost, and cost-effectiveness.

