### Statistical analysis

Data will be primarily analyzed according to the intention-to-treat principle. Patients with protocol violations will be followed up, and data will be recorded. Data will be analyzed with and without inclusion of patients with protocol violation. At baseline, differences in baseline characteristics will be compared between the intervention and control group in order to assess comparability between the two groups. Student's T-test (parametric numeric data), Mann-Whitney U-test (nonparametric numeric data) or Chi-square test (categorical data). Data will be presented as mean ± SD (parametric data) or medians and percentiles (non-parametric data).

The hazard ratio for falling will be calculated using a Cox-regression model. Herein, the time between the intervention (*i.e*., drug assessment/change or not) and the first and/or second fall will serve as the primary outcome measure. Fallers will be defined as those who will fall once or more during the one-year follow-up. Differences in cumulative incidence of falls will be analyzed using log-linear or Poisson regression, adjusted for over dispersion because of interdependence among the dependent variable (falls). Differences in adverse health effects between both trial arms will be assessed using Chi^2 ^testing. Several subgroups will be distinguished in order to examine whether the effect of the intervention depends upon sex, age, race and risk of future falls. Since healthcare costs per patient are typically highly skewed, non-parametric techniques will be used to derive a 95% confidence interval for the differences in distributions of the costs. In a sensitivity analysis the impact on cost-effectiveness of statistical uncertainty on the main study outcomes will be determined (uni- and multi-variable).

The association between genetic polymorphisms and falls history will be evaluated using a multivariate logistic regression analysis. A *p*-value of < 0.05 will be used as threshold for statistical significance.

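### The between-arm chi-square test of adverse health effects is open to ascertainment bias: extra nurse calls about negative effects are described only for the intervention, and the test is not limited to data collected alike in both arms

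*Protocol article*

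**What the plan says.** All references are to the protocol article.

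- **Intervention.** After the text on changing drugs, which "will be stopped, reduced or substituted with potentially safer drugs in the intervention group", the section adds that a research nurse is to counsel patients and "evaluate possible negative effects by weekly telephone calls over a period of 1 month". Problems found are then discussed with the clinical investigator and the geriatrician.
- **Procedure.** For the comparator, "in the 'care as usual' group no (medication) change will be made". No weekly calls are described for this arm. Table 1 does not list the calls. It does have a row for complications at 3, 6, 9 and 12 months, with no distinction of arm.
- **Outcome measures.** The secondary outcomes include "positive or negative health effects, cost, and cost-effectiveness".
- **Statistical analysis.** "Differences in adverse health effects between both trial arms will be assessed using Chi"-square testing. The source of the events is not named.
- **Randomization.** Neither patients nor the geriatrician can be blinded.

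**The concern.** A simple comparison of proportions is fair only if an event has the same chance of being recorded in each arm. Here one arm is asked about negative effects about four extra times in the first month, when drugs are being changed. If complaints heard on those calls count in the chi-square test, the intervention arm can show more adverse effects with no true difference.

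Harm is central to any judgement about drug withdrawal, and the Discussion says that the results should inform clinicians and policymakers. A spurious excess could discredit a useful intervention. A real excess could be dismissed as a product of closer questioning. Once events from the two sources are mixed without a flag, the data cannot separate these explanations.

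**Working it through.** The plan gives no figure for this comparison, so there is none to reproduce. The check compares the collection channels and then illustrates how much the difference could matter.

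**Channels, arm by arm**

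| Channel | Intervention | Care as usual |
|---|---|---|
| Complications record, months 3, 6, 9, 12 (Table 1) | yes | yes |
| Hospital records (Costs) | yes | yes |
| 12-month visit with medical history (Follow-up) | yes | yes |
| Weekly nurse calls, month 1 (Intervention) | yes, about 4 | none described |

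That only one arm is called is an inference, but a strong one. The sentence stands in the Intervention section, follows the steps for changing drugs, and covers one month, the same length as the dose-reduction period. Controls have no drug change to be counselled on.

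**Illustration**

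Inputs from the Sample size calculation section: 310 per arm and 15% drop-out, so 310 × 0.85 = 263.5, taken as 263. The two-sided 0.05 level follows the significance threshold in the Statistical analysis section.

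Assumptions, none of them from the document:
- The true risk p of an adverse effect is the same in both arms (10% to 30%).
- The common sources detect a share q of events in either arm (50% to 80%).
- The calls detect every event in month 1.
- A share f of events falls in month 1 (1/12 if spread evenly, or 1/3 if concentrated early).
- Call findings are counted in the test.

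Formulas:
- Detection in controls: s_C = q. Detection in the intervention arm: s_I = f + (1 − f)q.
- Observed risks: p_I = p·s_I and p_C = p·s_C. Apparent risk ratio: s_I/s_C.
- With d = p_I − p_C, pooled SE0 and unpooled SE1, P(significant) = Φ((d − 1.96·SE0)/SE1) + Φ((−d − 1.96·SE0)/SE1).

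One case in full, with f = 1/3, q = 0.5 and p = 0.30:
- s_I = 1/3 + (2/3)(0.5) = 0.667, so p_I = 0.20, p_C = 0.15 and d = 0.05.
- SE0 = √(2 × 0.175 × 0.825/263) = 0.0331.
- SE1 = √((0.20 × 0.80 + 0.15 × 0.85)/263) = 0.0331.
- (0.05 − 1.96 × 0.0331)/0.0331 ≈ −0.45, and Φ = 0.33. The other tail is negligible.

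| f | q | Apparent risk ratio | False-positive rate, p = 10% | p = 30% |
|---|---|---|---|---|
| 1/12 | 0.8 | 1.02 | 0.051 | 0.052 |
| 1/12 | 0.5 | 1.08 | 0.055 | 0.068 |
| 1/3 | 0.8 | 1.08 | 0.06 | 0.08 |
| 1/3 | 0.5 | 1.33 | 0.13 | 0.33 |

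If the test uses only the common sources and these detect equally, then s_I = s_C. The apparent risk ratio is 1.00 and the rate stays at 0.05.

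**The case against.** The strongest case against is that the calls look like patient care rather than outcome collection. They come with counselling, their findings go to the treating team, and they appear neither in Table 1 nor in the Measurements and Follow-up text. Table 1 has its own complications row for everyone. On that reading the chi-square test already rests on a common record. Naming the source form is also a detail that a condensed article may leave to the full protocol or analysis plan.

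Much of this stands. A reader might infer that the comparison is biased as a matter of fact, but the document does not support that, because it never says that call findings enter the test. It does not say that they stay out either. The article itself fixes both the between-arm test and a channel for harms in one arm only, so the exposure comes from what is stated and is more than missing detail.

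A reader might also infer a very large error by counting eight solicitations against four. If each contact independently drew a complaint with probability 2%, the reported risks would be 1 − 0.98^8 = 14.9% and 1 − 0.98^4 = 7.8%, and the test with 263 per arm would be falsely significant 74% of the time. That model gives a call covering one week the same weight as a report covering three months, and it lets calls generate complaints instead of detecting events. The document supports neither assumption, so 74% should not be taken as the size of the problem.

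The concern does not extend to the primary outcome. Falls are based on the Falls Calendar, which all participants receive.

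**Conclusion.** The point holds as a conditional one: as written, the comparison of adverse health effects is open to unequal ascertainment, and the direction would be against the intervention.

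The size cannot be determined from the document. With no true difference and 263 per arm, the false-positive rate is close to nominal (about 0.05 to 0.07) if the calls only improve detection of first-month events and events are spread evenly over the year. It reaches 0.13 to 0.33 if a third of events fall in month 1 and quarterly reports detect half. It would be higher if each call elicited complaints independently. Clustering of events in month 1 is plausible while drugs are being changed, but it remains an assumption. All these figures also assume that call findings are counted in the test.

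This concerns a secondary outcome and is cheap to correct. It should be settled before the harm data are compared.

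**What to change.** State in the Statistical analysis section that the between-arm test of adverse health effects uses only sources with the same method and schedule in both arms: the Table 1 complications record at 3, 6, 9 and 12 months, hospital records, and the 12-month visit. Record the source of each event. Report events known only from the weekly calls descriptively for the intervention arm, without a test.

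The cost is one sentence and a source flag per event. The calls themselves and patient care do not change. The downside is that mild early effects heard only on the calls leave the comparative table, although they are still reported. The restriction reduces the risk but may not remove it: in an unblinded trial, patients who were called may recall and report more at month 3, and the report of results should say so.
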